# Scopolaminebutyl given prophylactically for death rattle: study protocol of a randomized double-blind placebo-controlled trial in a frail patient population (the SILENCE study)

**DOI:** 10.1186/s12904-018-0359-4

**Published:** 2018-09-07

## Abstract

**Background:**

Death rattle (DR), caused by mucus in the respiratory tract, occurs in about half of patients who are in the dying phase. Relatives often experience DR as distressing. Anticholinergics are recommended to treat DR, although there is no evidence for the effect of these drugs. Anticholinergic drugs decrease the production of mucus but do not affect existing mucus. We therefore hypothesize that these drugs are more effective when given prophylactically.

**Methods:**

We set up a randomized double-blind, placebo-controlled, multi-center study evaluating the efficacy of prophylactically given subcutaneous scopolaminebutyl for the prevention of DR in the dying phase. The primary outcome is the occurrence of DR defined as grade ≥ 2 according to the scale of Back measured by a nurse at 2 consecutive time points with an interval of 4 h. Secondary outcomes include adverse effects, quality of dying, quality of life in the last three days and bereavement. A sub-study will explore the experience of participating in a clinical trial in the dying phase from the perspective of relatives. Four hospices will include 200 patients.

**Discussion:**

This is the first double-blind placebo-controlled study to prevent DR in patients in the hospice setting. Research in dying patients is challenging. We will apply ethical and organizational strategies as suggested in the literature.

**Trial registration:**

The trial is retrospectively registered in the Dutch Trial register, identifier NTR 6438 June 2017. EudractCT number 2016–002287-14.

Anticholinergic medication is considered the standard treatment for death rattle. Treatment of death rattle is regarded as an essential intervention in the care of dying patients by specialists in palliative care [8]. However, evidence for the efficacy of anticholinergics is scarce. Until now, two randomized placebo-controlled trials on anticholinergics for the treatment of death rattle have been published, both with important limitations. One study was clearly underpowered with the inclusion of seven patients [7], whereas the other study only used a single dose of the short-acting anticholinergic drug atropine [8]. Both trials found no differences in the intensity of death rattle and side effects between patients receiving anticholinergics and placebo. Another study compared the efficacy of three different anticholinergic drugs and found no differences between the drugs on the presence and intensity of death rattle [9]. The Dutch guideline on care for dying patients is cautious in advising the use of medication to treat death rattle [1]. Its recommended approach involves awareness, posture changes in bed and extensive pro-active explanation to and communication with relatives. Only if the rattle is still perceived as burdensome by relatives, anticholinergics may be considered.

Anticholinergics decrease the production of mucus but do not affect existing mucus [10]. These drugs may therefore be more effective if they are administered prophylactically [9–11], before death rattle occurs. [12] Scopolaminebutyl is the most frequently prescribed anticholinergic drug for death rattle in the Netherlands. We therefore designed a randomized controlled trial (RCT) to answer our research question: is scopolaminebutyl, when given prophylactically, effective in preventing death rattle? In this paper, we describe the protocol for this study and show how we addressed the medical-ethical rules and Good Clinical Practice guidelines [13] for this vulnerable patient population.

To perform an RCT in patients in the dying phase is a challenge. First, people in the last stage of their lives can be considered vulnerable and the ethics of asking vulnerable patients to participate in research is still a topic of debate [14–16]. Secondly, including sufficient numbers of patients has been demonstrated to be a challenge in palliative and end-of-life care research [17, 18]. And finally, a recent review showed that gatekeeping is a serious threat to performing research in palliative care [19]. We used several strategies that were suggested in the literature to address these problems.

## Methods

### Study design

The SILENCE study is a randomized double-blind, placebo-controlled, multi-center study to measure the efficacy of prophylactically administered scopolaminebutyl in the prevention of death rattle in the dying phase. This study will be conducted in four hospices. The trial is designed in accordance with the Good Clinical Practice guidelines and according to the general ethical principles outlined in the Declaration of Helsinki [13]. The trial is retrospectively registered in the Dutch Trial register, identifier NTR 6438; EudractCT number 2016–002287-14. The study incorporates a sub-study: a questionnaire will be sent to relatives to gain insight in how they experienced participation of their beloved one in research.

### Study population

Patients who are admitted to one of the participating hospice facilities will be asked for participation. Inclusion and exclusion criteria are described in Table 1. When the multidisciplinary team agrees that the dying phase has started, exclusion criteria will be checked again to see whether the patient is still eligible to participate.

**Table 1 Tab1:** Inclusion/exclusion criteria

Inclusion criteria	Exclusion criteria
Patient is admitted to one of the participating hospices	Patient shows signs of active respiratory infection
Patient is aware that the admission will be up to death	Patient has a tracheostomy or tracheal cannula
Patient’s life expectancy at admission is at least 3 days	Patient uses systemic anticholinergic drug(s) or octreotide (at admission or when the dying phase starts)
Patient shows no signs of disturbed consciousness	Patient has death rattle grade 1 or higher on the scale of Back at the start of the dying phase.

### General procedure

#### Regular hospice care

In the Netherlands, patients who are admitted to a hospice facility in principle have a life expectancy of less than three months and stay there until death. Standard procedure at admission includes an interview about their symptoms, care needs and expectations, by both a doctor and a nurse.

Marking of the start of the dying phase, the last 2–5 days of life, is based on recognition of a number of signs by the nurses and doctors of the hospice: the patient is bedbound, only able to take sips of fluid, no longer able to swallow and take oral medication, and/or subcomatose.

When this state is recognized, the patient and his family are informed that death is imminent and they receive explanation about the care given in these last days and what symptoms might occur. They also receive a leaflet with written information. The recognition of the dying phase is a signal to start the Care Program for the Dying (CPD). The CPD is a digital, structured template for care in the last days and hours of life. This template defines goals of care in all four domains of palliative care (e.g. on pain, dyspnea, restlessness, nausea, death rattle, oral hygiene, needs of family on psychological/spiritual domain, needs of the patients on psychological/spiritual domain). The nursing staff evaluates these aspects of care and symptoms every four hours. They report their observations in the CPD. The observations are continued until the patient dies. The CPD is standard of care in the hospice facilities that participate in this study.

#### Study

For this study, standard care procedures in the hospice facilities are extended with some extra steps:At admission: the doctor assesses if the patient meets the inclusion criteria of the study. If so, the patient is informed about the study and invited to think about participation. Written information will be given. After a period for reflection (maximum 48 h), the patient will get the opportunity for asking additional questions and, if he/she is willing to participate, to sign the informed consent form. The patient and family are aware of the fact that the study will not start immediately, but at the moment the dying phase is recognized. The doctor also informs the patient and relatives about the questionnaire which will be sent to relatives three months after the death of the patient.Start of the dying phase: the actual study (the intervention) starts with the recognition of the dying phase. The exclusion criteria will be checked again. In case of eligibility, the first dose of the study medication scopolaminebutyl 20 mg (=1 ml) or placebo (=1 ml NaCl 0.9%) will be administered subcutaneously. The study medication will be provided four times a day. The study medication is packed in numbered boxes.Care program: the CPD is extended with extra observations related to the study. The extra observations include restlessness, scored according to the Vancouver Interaction and Calmness Scale (VICS score) [20] and death rattle, scored according to Back [4]. Nurses also report on the oral care given.Relatives: three months after a patient’s death, relatives will be sent a questionnaire.

#### Integration of study procedures into regular care

The study procedures have been discussed with the medical and nursing staff of the participating hospices to assure integration of the study logistics in regular care procedures. These procedures are largely similar for the different hospices, but differ regarding the admission process, contacts with pharmacists and procedures after death. Standard care is given according to the guidelines of the Netherlands Comprehensive Cancer Organization. Only few adjustments were needed in the procedures around the recognition of the dying phase and the care given in the last days of life (e.g. oral care, posture changes when (death) rattle starts, symptom management). Staff of the hospices have much experience in recognizing the dying phase and in working with the CPD. All personnel has been involved in previous clinical studies.

#### Training hospice staff

The multidisciplinary teams received a training about GCP. Further, they were trained on site in implementing the study protocol, procedures and data management. The primary researcher ([name]) provided this training on site.

#### Substudy

Relatives will be sent a questionnaire three months after the death of the patient. This questionnaire consists of several general questions (demographic and non-demographic), questions about the patient’s quality of life and quality of death, the Dutch version of the inventory of traumatic grief (ITG) [21] and questions about how participation of the patient in the study affected the quality of care according to the relative. Relatives will also be invited to take part in in-depth interviews about their experience of participating in research in the dying phase.

### Informed consent procedure

When a patient meets the inclusion criteria, he/she will be informed about the study and asked to participate. A patient information leaflet (PIL) is provided and time is given to consider participation. After 48 h, the patient can ask further questions and is asked for consent. When the patient agrees, the PIL is signed twice, with one copy for the patient and one for the researcher. Patients are free to withdraw from the study at any moment after signing informed consent.

### Intervention

When the start of the dying phase is recognized, study medication (scopolaminebutyl 20 mg (=1 ml) or placebo (=1 ml NaCl 0.9%)) will be given four times a day subcutaneously. Treatment will be continued until death or until the occurrence of death rattle with a severity of grade ≥ 2 according to the scale of Back [4] at two consecutive measurements with an interval of 4 h. In the latter case, medication will be regarded as “not effective” and the study medication will be withdrawn. The patient will then further receive care as usual.

### Randomization

Block randomization with varying block sizes of 2–4 is applied to create a randomization list for the study medication (verum or placebo) within each center (i.e. randomization is stratified by center).

As a result, verum and placebo are equally distributed over both patients and sites.

### Outcome measures

#### Primary outcome

The percentage of patients who develop death rattle, defined as the occurrence of death rattle with a severity of grade ≥ 2 according to the scale of Back at two consecutive measurements with an interval of 4 h.

#### Secondary outcomes

Time from the recognition of the dying phase until the occurrence of death rattle (in hours)Occurrence of adverse events, i.e. urinary retention, dry mouth and restlessnessQuality of life during the last three days of life and quality of dying, both according to the attending nurse and relativesBereavement of relativesExperience of relatives concerning the patient’s participation in a (double-blind, placebo-controlled) clinical trial

### Measurement instruments

Table 2 provides an overview of measurement tools used in the SILENCE study.

**Table 2 Tab2:** Measurement tools

	Measurement tool
Death rattle	Scale of Back: 0 = no rattle, 1 = audible close to the patient, 2 = audible standing at the end of the bed, 3 = audible standing in the door opening [4]
Restlessness	Vancouver Interaction and Calmness Scale (VICS score): 5 questions about restlessness scored on a 6-point Likert scale [20]
Dry mouth/urinary retention	Reported observations in CPD (agreed standards, implemented for this study)
Grief	Inventory of Traumatic Grief: 30 questions about grief [21]
Quality of life	Numeric rating scale (0 = worst quality – 10 = best quality) [22]
Quality of dying	Numeric rating scale: 0 = worst quality – 10 = best quality); 15 qualitative descriptions (peaceful, quiet, shocking, painful, etc.) [22] to tick.

### Data collection

Data collection starts when the dying phase starts and the CPD is implemented. Collection of patient-related information will be continued until death. All data will be collected on electronic case report forms using ALEA™, an online electronic database application as implemented by the Clinical Trial Center of the Erasmus MC Cancer institute (CTC).

### Sample size calculation

For the power calculation we used data from a previous study. In a sample of 400 deaths, 39% of the patients developed a death rattle with a severity of grade ≥ 2 according to the scale of Back (personal communication). We aim to reduce the occurrence of death rattle from 39 to 19%. Given a two-sided significance level of 0.05 and 80% power, a total of 180 patients are required based on a continuity-corrected Chi-square test. Taking into account that 10% of the patients who have given informed consent are expected to drop out before the actual start of the study because of sudden death or the occurrence of exclusion criteria, 200 patients are needed in total. Turnover in the four hospice settings is high: in the first three months of 2015, 120 patients were admitted, that is about 480 per year. Based on a 40% participation rate (= 192 out of 480), recognition of the dying phase and application of the CPD in 80% of all consenting patients(= 153 of 192) and a drop out of 10% it is possible to include approximately 140 patients in a year. This means that an inclusion period of approximately 18 months is needed.

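### The sample size section uses two incompatible losses between consent and start (10% and 28%), so it does not fix whether the target of 200 counts consented or started patients

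*Protocol article*

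**What the plan says.** The Sample size calculation section takes a control rate from earlier data, in which "39% of the patients developed a death rattle with a severity of grade ≥ 2 according to the scale of Back", and sets the aim: "We aim to reduce the occurrence of death rattle from 39 to 19" percent. "Given a two-sided significance level of 0.05 and 80% power", it concludes that "a total of 180 patients are required based on a continuity-corrected Chi-square test". It then raises 180 to 200 because "10% of the patients who have given informed consent are expected to drop out before the actual start of the study", giving sudden death and newly arisen exclusion criteria as the reasons.

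The same section then estimates accrual. It starts from 480 admissions a year and applies 40% participation (192 consents). Next comes "recognition of the dying phase and application of the CPD in 80% of all consenting patients" (153 patients), then a drop-out of 10%, which leaves about 140 a year. From this it derives an inclusion period of roughly 18 months.

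The abstract says only "Four hospices will include 200 patients". The General procedure section, under Study, places the start of the intervention at recognition of the dying phase, with exclusion criteria rechecked at that point.

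**The concern.** Both steps describe what happens between consent and the first dose, but they lose different fractions of the same people. A consenting patient whose dying phase is never recognised cannot start study medication, so the 20% in the accrual step is a pre-start loss just as the 10% is. The inflation from 180 to 200 leaves it out.

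As a result, 200 is a number of consents in the inflation sentence and behaves as a number of started patients by the end of the section. A trial team could close recruitment on either count in good faith. One choice leaves the trial short of the 180 patients that the plan says it needs. The other randomises 20 more dying patients than the calculation calls for (200 − 180).

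**Working it through.** **Inputs.** Rates 0.39 and 0.19, two-sided alpha 0.05, 80% power, continuity-corrected chi-square, 10% pre-start loss, and the accrual figures 480, 40%, 80% and 10% all come from the Sample size calculation section. Equal allocation comes from the Randomization section ("verum and placebo are equally distributed over both patients and sites").

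**1. The plan's sample size reproduces.** With p̄ = 0.29 and d = 0.20:

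- Uncorrected: n′ = [1.960·√(2·0.29·0.71) + 0.842·√(0.39·0.61 + 0.19·0.81)]² / 0.20² = 79.6 per arm.
- Corrected: n = (n′/4)·[1 + √(1 + 4/(n′d))]² = 89.3, rounded up to 90 per arm, or 180 in total.
- Inflation: 180/0.90 = 200.

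**2. The accrual figures reproduce.** 480 × 0.40 = 192 consents; × 0.80 = 153.6; × 0.90 = 138.2 a year (the plan rounds to about 140). The share of consenting patients who start is 0.80 × 0.90 = 0.72, a loss of 28%.

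**3. Which count fits 18 months?**

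- 200 consents: 200/192 × 12 = 12.5 months.
- 200 patients after both losses: 200/138.2 × 12 = 17.4 months.
- Running a full 18 months: 192 × 1.5 = 288 consents and 138.2 × 1.5 = about 207 started.

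**4. Power under each reading.** Uncorrected power with n per arm is Φ{[d√n − 1.960·√(2·0.29·0.71)] / √(0.39·0.61 + 0.19·0.81)}. For corrected power, n is replaced by the n′ that solves the correction formula in step 1, which is n′ = n − 2/d + 1/(d²n). For 72 per arm, n′ = 72 − 10 + 0.35 = 62.35, and power is Φ[(0.20·√62.35 − 1.258)/0.626] = Φ(0.51) = 69.6%.

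| What is counted | Started | Corrected power | Uncorrected power |
|---|---|---|---|
| 200 consents, 28% loss | 200 × 0.72 = 144 | 69.6% | 75.9% |
| 200 consents, the 10% lying wholly inside the 20% | 200 × 0.80 = 160 | 74.9% | 80.2% |
| 180 started (the stated design) | 180 | 80.3% | 84.7% |
| 200 started | 200 | 84.8% | 88.2% |

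Exact binomial enumeration at 72 per arm gives 70.5% with the corrected test and 76.7% without the correction. Under the rule in the Primary study parameter analysis section (chi-squared, or Fisher when cells are small) it gives 76.5%.

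**5. Consents needed for 180 started patients.** 180/0.72 = 250. At 138.2 starts a year this takes 180/138.2 × 12 = 15.6 months.

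**The case against.** A reader might infer that the trial will end with 144 treated patients and 70% power. The documents do not support that. It requires recruitment to close at 200 consents, and no section states such a rule. The accrual step counts patients as included only after both losses, and the abstract uses the same verb for the 200. The 18 months fits 200 started patients. The Conclusion section expects completion within two years of April 2017, which does not suggest stopping after 12.5 months of consents. On this reading the trial exceeds 80% power.

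The 70% is also tied to the continuity-corrected test. The primary analysis names a chi-squared test without a correction, and under that rule the worst case is about 76%, some 3 to 4 points short of 80%.

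A third reading is possible. The 10% may be the same 10% in both steps, applied after the 80% filter. Then 200 counts patients who reach the care program, 200 × 0.90 = 180 start, and this takes 200/153.6 × 12 = 15.6 months. Against it, the inflation sentence takes its 10% from patients who have consented, not from those who have reached the care program.

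Finally, no individual figure is miscalculated; every one reproduces within rounding.

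These points limit the consequence, but they do not remove the inconsistency. The section states both losses and both results, so condensation from a fuller protocol does not explain it.

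**Conclusion.** The point holds as an internal inconsistency. The loss between consent and start is 10% in one step and 28% in the other, and the meaning of 200 shifts from consents to started patients. A loss of power is conditional on which count closes recruitment:

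- At 200 consents, about 144 patients start, with about 70% corrected or 76% uncorrected power.
- At 200 started patients, which the timeline favours, corrected power is about 85%, and the pre-start allowance has been applied to people who have already started.

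Neither of these gives the stated design of 180 started patients at 80% power. The figures assume the plan's event rates, its attrition rates and an equal split between arms. They also treat the 80% and the second 10% as successive losses, as the accrual arithmetic does.

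**What to change.** Define the target as 180 patients randomised and started on study medication, and close recruitment on that count and not on consents. Use one consent-to-start loss in both the inflation and the accrual step. At the plan's own 28%, restate the expected number of consents as about 250, and give the abstract's target in the same unit.

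If the sponsor prefers to keep 200 as a count of consents, restate the expected analysed number as about 144 and the power accordingly, naming the test to which that power refers.

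The cost is a wording amendment and a larger stated number of consents. At the plan's own rate, 180 starts take about 15.6 months, within the 18 months already planned.

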### Statistical analysis

All analyses will be performed in the most recent version of IBM SSPS Statistics or Stata. Analyses will follow the intention-to-treat principle. However, patients initially randomized but considered ineligible afterwards based on information that should have been available before randomization, will be excluded from all analyses. A *p*-value < 0.05 is considered to indicate statistical significance.

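### Randomised patients later judged ineligible leave every analysis, safety included; keep them in and move the exclusion to a sensitivity analysis

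*Protocol article*

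**What the plan says.** The Statistical analysis section of the protocol article sets the principle: "Analyses will follow the intention-to-treat principle". The next sentence qualifies it openly: "patients initially randomized but considered ineligible afterwards based on information that should have been available before randomization, will be excluded from all analyses". It names no separate population for safety. The adverse events listed under Secondary outcomes (urinary retention, dry mouth, restlessness) are compared between arms under Secondary study parameters analysis, so the exclusion reaches them too.

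Table 1 under Study population lists this exclusion criterion: "Patient has death rattle grade 1 or higher on the scale of Back at the start of the dying phase". The primary outcome uses the same scale: grade 2 or higher at two consecutive measurements 4 hours apart. Under General procedure, Study, eligibility is reviewed again before the first dose: "The exclusion criteria will be checked again". The Study design section describes the trial as double-blind.

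**The concern.** Two separate things are at stake.

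**Efficacy.** The exception restricts the subject of the information but not when it was written down or judged. A fact that ought to have been known before randomisation can still be asserted after the outcome has been seen. For most criteria in Table 1, such as a tracheostomy or use of an anticholinergic, this matters little. For baseline rattle it may matter, because a patient who rattles soon after the first dose is a natural candidate for doubt about whether grade 0 was correct at the start. Concealing the arm does not conceal the rattle. If the drug prevents rattle, early rattlers are mostly on placebo. Removals that depend on rattle would then take away mainly placebo events and shrink the observed effect.

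**Safety.** A patient who received study medication and had an adverse event would leave the safety comparison because of an eligibility judgement. This holds even if every such judgement is fair and blind.

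**Working it through.** **Inputs.** From Sample size calculation: "We aim to reduce the occurrence of death rattle from 39 to 19" per cent, and "Given a two-sided significance level of 0.05 and 80% power, a total of 180 patients are required based on a continuity-corrected Chi-square test". From Randomization: equal allocation ("verum and placebo are equally distributed over both patients and sites"). The article gives no number of exclusions after randomisation, so every such number below is an assumption.

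**1. The plan's own figure.** With p1 = 0.39, p2 = 0.19, d = 0.20 and mean rate 0.29:
- Uncorrected: n = [1.960·√(2·0.29·0.71) + 0.842·√(0.39·0.61 + 0.19·0.81)]² / 0.20² = 79.6 per arm.
- Continuity-corrected: n' = (n/4)·[1 + √(1 + 4/(n·d))]² = 89.3, so 90 per arm and 180 in total.
- Dropout: 180 / (1 − 0.10) = 200.

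Both stated totals reproduce. There is no numerical error here.

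**2. Effect on power.** The 10% allowance covers losses before the study starts, not removals after dosing. Continuity-corrected power is Φ{[d − 1/n − 1.960·√(2·0.29·0.71/n)] / √[(0.39·0.61 + 0.19·0.81)/n]}:

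| Analysed per arm | Assumed removal | Power |
|---|---|---|
| 90 | none | 80.3% |
| 86 | about 5% | 78.3% |
| 81 | 10% | 75.5% |

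**3. Effect on a result, with removals of placebo events only.** Pearson chi-squared, placebo vs active. The primary analysis section does not say whether the test is continuity-corrected, so both versions are shown.

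| Case | Data | p, uncorrected | p, corrected |
|---|---|---|---|
| Borderline | 30/90 vs 18/90 | 0.043 | 0.064 |
| one removed | 29/89 vs 18/90 | 0.056 | 0.081 |
| two removed | 28/88 vs 18/90 | 0.072 | 0.103 |
| Borderline if corrected | 31/90 vs 18/90 | 0.029 | 0.044 |
| one removed | 30/89 vs 18/90 | 0.038 | 0.057 |
| Planned effect | 35/90 vs 17/90 | 0.003 | 0.005 |
| two removed | 33/88 vs 17/90 | 0.006 | 0.009 |
| eight removed | 27/82 vs 17/90 | 0.035 | 0.053 |
| ten removed | 25/80 vs 17/90 | 0.062 | 0.092 |

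The planned-effect counts are 0.39·90 = 35.1 and 0.19·90 = 17.1, rounded. A single removal can cross 0.05 under either version of the test, but only from a starting point chosen to lie close to it. At the planned effect it takes about ten placebo-event removals uncorrected, or eight corrected.

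**4. If the drug has no effect.** A simulation of 20,000 trials per setting used 39% in both arms, 90 per arm and the uncorrected test. Removing equal numbers of rattlers from each arm gave no mean bias. Removing 2, 4, 6 or 9 rattlers from one arm only gave type I error of about 5.6%, 7.4%, 9.7% or 16.4%. Those one-sided figures need removals that depend on arm as well as outcome.

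**The case against.** The case for leaving the rule alone has real force.

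- **The exception is declared.** A reader might infer that the plan contradicts itself by claiming intention to treat and then abandoning it. It does not: the principle is stated and openly qualified, and the grounds are confined to facts that predate randomisation.
- **There are safeguards.** The trial is double-blind, and the criteria are reviewed again before the first dose. Late discoveries should be uncommon, and decisions would ordinarily be made without knowing the arm. A reader might infer unblinded exclusions and inflated type I error. The document does not support that, and the one-sided simulation figures do not describe what this design makes likely.
- **Procedure may sit elsewhere.** Who decides on ineligibility, when, and how this is documented is detail that an article may leave to the full protocol. Its absence here is not a fault.
- **The assessor is not documented.** It is tempting to say that the same nurses score baseline and outcome. The abstract says a nurse measures the outcome, but the eligibility check names no assessor.
- **The bias is conditional.** It needs removals that depend on early rattle and a drug that works, and it then runs towards no effect.

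What remains is the rule itself. The article fixes removal from all analyses, so this is a choice made rather than a detail left out. Double-blinding hides the arm but not the outcome. None of these points answers the loss of dosed patients from the safety comparison.

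**Conclusion.** The concern stands in a limited form. The rule departs from intention to treat for every analysis, and its wording allows eligibility to be reconsidered in hindsight on a criterion that shares its scale with the primary outcome. If the drug works and such removals follow early rattle, the effect estimate would be biased towards no effect. Both conditions are assumptions, and the number of exclusions is not given, so the size cannot be stated.

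A reader might infer that one or two late exclusions would overturn the trial. That is true only of a borderline result. The 30/90 vs 18/90 example is itself already non-significant with the continuity correction (p = 0.064), and at the planned effect two removals leave p at 0.006 uncorrected. The safety part does not depend on these assumptions: as written, dosed patients judged ineligible are not counted in the adverse event comparisons.

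This is a cheap improvement, not a flaw that threatens the trial.

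**What to change.** Replace the exception in Statistical analysis with two or three sentences:

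- The primary analysis includes all randomised patients who started study medication, in their allocated arm. This is still a modified set, but in a double-blind trial starting the first dose should not depend on the arm, and it precedes any outcome under treatment.
- Safety analyses include all dosed patients.
- Excluding patients found ineligible is a sensitivity analysis only, based on records dated before the first dose and decided blind to arm and outcome.

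The cost is a small change of text and one extra analysis. The downside is that a few ineligible patients may slightly dilute the effect; the sensitivity analysis would show how much.
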